#### Outcome measures

Mobility, strength and balance (static and dynamic) are all equally important physical attributes for an older person to maintain when living independently. We therefore determined it was more appropriate to calculate a cumulative score of the four physical tests, rather than choose just one, as the primary outcome measure (see Data analysis for more detail).

Secondary outcome measures included: functional reach; falls efficacy scale; sit-to-stand 1 and 5 times; activities specific balance scale; timed up and go; vitality plus scale; tandem walk; the Late Life Function and Disability instruments; and, number of home care services received. These measures (see Table 1) were administered at baseline, eight weeks and six month follow-up. The six month follow-up was important because often exercise programs are not maintained once a service has finished and the Care Manager is no longer there to remind the client of the importance of doing their exercises. This would also show which exercise program, if any, was continued over the longer term.

As described earlier, to determine each client’s exercise frequency they were given a calendar and asked to simply tick each day that they performed the exercises during the trial period. Other data collection techniques for determining compliance were tested during the pilot study [8], such as using clickers twice a week to count the number of times an assigned activity was completed (e.g. Tuesday 10 one leg balance exercises were completed and 15 on Thursday). However, none were found to be successful, whereas getting the client to tick a calendar each day was considered to be more achievable. The number of falls was measured by self-report at baseline and six month follow-up by asking how many falls have you had in the past 6 months. For each individual the study lasted six months, recruitment was expected to be completed within six months and data collection completed twelve months from commencement of recruitment.

### Data analysis

Data will be analysed using the Statistical Package for the Social Sciences computer statistical software, version 19 [24]. Both *intention-to-treat* (ITT) and *per protocol* (PP) analyses will be performed. For each outcome measure, we will calculate the change that has occurred during the intervention period by subtracting the baseline from the 8-week values. Where the distribution of the change is approximately normal, an independent *t*-test will be used to compare the groups. When the data are not normally distributed a Mann-Witney U test will be used. Categorical data will be analysed using a Chi-square test.

The summary variable to be used as the primary outcome measure will be created using clients’ functional reach, chair sit to stand, timed up and go and tandem walk scores. A factor analysis will be carried out to identify the relative importance of these four variables in the dataset, at baseline. This analysis will produce a set of factor loadings or ‘weights’ that can then be used to construct the new summary variable (as a weighted linear combination of the four separate measures above). The weights will be scaled so that, at baseline, the mean of the summary variable is zero and its standard deviation is 1. The same linear combination will be applied to create the summary variable at 8-weeks. Any change in the summary variable over the 8-week period will be assessed for statistical significance in exactly the same manner as the other outcome variables (as described above).

Analyses of the post-testing results at 6 months will consist of a regression model for the outcome of interest, adjusting for the correlations due to the multiple measurements on each individual by treating the person ID as a random effect. Multiple linear regressions will be used to identify any differences between the groups at initial data collection, eight weeks and six months, and to examine differences between the groups in terms of change in measures over the follow up period. A p value of <0.05 will be considered statistically significant. Data analysis will be supervised by a statistician who is not involved in conducting the trial.

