### Sample size

The sample size was calculated based on 80% power, a 5% significance level and a ‘medium’ effect size of 0.5 [11] related to the two groups, using as the primary outcome, a composite measure incorporating balance, strength and mobility. This effect size was considered sufficient to recommend a change in practice, given that functional improvement is also expected in the current practice group. Based on Peat [12] a sample size of 64 in each group is indicated. Allowing for a 12% drop out rate as found during the pilot study [8], approximately 75 participants in each group were needed, or 150 in total.

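### The primary 8-week test is an unadjusted comparison of change scores; regressing the 8-week composite on arm and baseline would be more precise at no cost

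*Protocol article*

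**What the plan says.** The Data analysis section of the protocol article sets the 8-week comparison for all outcomes: "For each outcome measure, we will calculate the change that has occurred during the intervention period by subtracting the baseline from the 8-week values". If the change looks approximately normal, the arms are compared by an independent t-test; otherwise, "When the data are not normally distributed a Mann-Witney U test will be used". The primary outcome is a weighted sum of four physical tests, scaled to mean 0 and SD 1 at baseline. The same weights are applied at 8 weeks, and the change is tested in the same way as for the other outcomes. No covariate is named for this test.

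Regression appears later in the section. A random-effects model is planned for the 6-month results, and "Multiple linear regressions will be used to identify any differences between the groups at initial data collection", at 8 weeks and at 6 months. These regressions name no covariates and are not said to replace the primary test.

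The Sample size section uses 80% power, a 5% significance level and an "effect size of 0.5 [11] related to the two groups", from which "a sample size of 64 in each group is indicated". It does not say which SD the 0.5 refers to (baseline, 8-week or change) and gives no baseline/8-week correlation.

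**The concern.** The baseline composite is measured before randomisation in every participant. A change score uses it with a fixed coefficient of 1. If the true slope of the 8-week score on baseline is below 1, as it is for equal SDs and r<1, subtraction over-corrects and adds noise that a fitted slope would remove. The plan therefore accepts a wider confidence interval than its own data can give.

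The choice of test also depends on the observed distribution, and the two branches address different quantities: a difference in mean change, or an ordering of changes. The planning argument is about the size of an effect ("This effect size was considered sufficient to recommend a change in practice"), so one model that always estimates a mean difference fits that purpose better.

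At stake are the precision of the primary estimate and, on one reading of the planning effect, whether the planned test reaches 80% power.

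**Working it through.** **Inputs from the protocol article.** Power 80%, alpha 5%, effect 0.5, 64 evaluable per arm, 12% dropout, 75 per arm and 150 in total (Sample size); composite SD of 1 at baseline, unadjusted test on change (Data analysis).

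**Assumptions.** Two-sided alpha (one-sided would give 50 per arm, which does not match 64); r from 0.3 to 0.8, because the article gives none; SD of 1 at 8 weeks as well as at baseline, relaxed in step 5. The one degree of freedom used by the covariate is ignored.

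**1. The plan's own figure.** A two-sample t-test with d=0.5 needs 63.8, so 64 per arm; power at 64 is 80.1%. Dropout: 64/0.88 = 72.7, so 73. The stated figure of about 75 leaves 75 × 0.88 = 66 per arm, with power 81.4%. The stated sample size is reproduced.

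**2. Precision.** With SD 1 at both visits:

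- Variance of change = 2(1−r).
- Residual variance after regression on baseline = 1−r².
- Ratio, adjusted to change = (1−r²)/[2(1−r)] = (1+r)/2.

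The ratio is 0.65 at r=0.3, 0.75 at 0.5, 0.85 at 0.7 and 0.90 at 0.8, so the variance is 35%, 25%, 15% and 10% lower.

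**3. Power at 64 per arm if 0.5 is in baseline-SD units.** The standardised effect is 0.5/√(2(1−r)) for change and 0.5/√(1−r²) for the adjusted model.

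| r | SD of change | Residual SD, adjusted | Power, change | Power, adjusted |
|---|---|---|---|---|
| 0.3 | 1.183 | 0.954 | 66.0% | 83.7% |
| 0.5 | 1.000 | 0.866 | 80.1% | 90.0% |
| 0.7 | 0.775 | 0.714 | 95.2% | 97.6% |
| 0.8 | 0.632 | 0.600 | 99.3% | 99.7% |

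The planned test falls short of 80% only when r is below 0.5.

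**4. Power at 64 per arm if 0.5 is in change-SD units.** The change test has 80.1% at every r. For the adjusted model the standardised effect becomes 0.5 × √(2(1−r))/√(1−r²), giving 93.6% at r=0.3, 90.0% at 0.5, 86.1% at 0.7 and 84.1% at 0.8.

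**5. Unequal SDs.** Let the 8-week SD be s and the baseline SD 1. The variance of change is 1 + s² − 2rs and the adjusted residual variance is s²(1−r²). Their difference is (1−rs)², which is never negative, so the ranking does not depend on equal SDs. The power levels do. With s=1.2 (an illustration) and an effect of 0.5 baseline SD, change versus adjusted power is 57%/69% at r=0.3 and 71%/77% at r=0.5.

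**The case against.** The best defence is that nothing here is invalid. A t-test on change is unbiased under randomisation and has the correct type I error, and its standard error already includes the variation from chance baseline imbalance. The normality rule is stated in advance, and its exact criterion may sit in a fuller plan. All of this stands.

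A reader might infer more than the article supports:

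- **That baseline is discarded.** It is not; it is subtracted.
- **That the trial is underpowered.** The Sample size section does not say which SD the 0.5 uses. In change-SD units, power is 80% whatever r is. In baseline-SD units with equal SDs, a shortfall needs r below 0.5, and no r is given.
- **That baseline adjustment guarantees 80%.** It does not if scores are more spread out at 8 weeks (step 5).
- **That imbalance biases the result.** Under randomisation it adds noise, not systematic error, and this is the same efficiency loss seen from another side.
- **That the Mann-Whitney branch prevents an effect size being reported.** Nothing stops a mean difference being given beside that test, and the composite is already in baseline-SD units.
- **That the planned baseline comparison does harm.** The article does not say that it steers the primary analysis.

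The later regressions, including one at 8 weeks, do not answer the point, because they name no covariates and do not replace the primary test. Nor is this a detail left out for brevity: the article states the unadjusted change-score test explicitly.

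**Conclusion.** The point holds as one of efficiency and clarity, not of bias or of a wrong sample size. The stated primary test is valid but less precise than a baseline-adjusted model. With equal SDs, the variance given up is 35% to 10% of the change-score variance for r from 0.3 to 0.8. In power at 64 per arm, adjustment adds about 18 percentage points at r=0.3, 10 at 0.5 and 2 at 0.7 if the 0.5 is in baseline-SD units, and about 14, 10 and 6 points if it is in change-SD units. Adjustment therefore helps under either reading, so the recommendation does not depend on which one was meant. The sizes rest on assumed values of r and on equal SDs; the direction rests on neither.

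**What to change.** Make the primary analysis a linear model of the 8-week composite on arm and baseline composite. Report the adjusted mean difference with a 95% CI whatever the distribution looks like. Replace the switch between t-test and Mann-Whitney with a bootstrap CI as the check on non-normality. Use the same model, each with its own baseline value, for the continuous secondary outcomes. In the Sample size section, state which SD the 0.5 refers to and the correlation assumed, if any.

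The cost is a change of analysis wording and minor programming. The baseline and 8-week measurements are already planned for both arms, and N=150 need not change.

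### The six-month model's single person random effect forces equal correlation between unequally spaced visits, so the test of baseline-to-six-month change can run above 5%

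*Protocol article*

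**What the plan says.** The Data analysis section describes two separate analyses.

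- **Eight weeks (primary).** Change is obtained "by subtracting the baseline from the 8-week values" and compared between groups by an independent t-test, or by a rank test if the change is not normally distributed. The composite primary outcome is handled in the same way.
- **Six months.** A regression model is used for each outcome, "adjusting for the correlations due to the multiple measurements on each individual by treating the person ID as a random effect". The following sentence plans regressions for group differences at initial data collection, eight weeks and six months, and for differences in change over follow-up. No random slope, other covariance structure or robust standard error is named. The threshold is the same throughout: "A p value of <0.05 will be considered statistically significant".

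Outcome measures places the visits at baseline, eight weeks and six months. Data to be collected puts the last visit four months after the restorative service ended.

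**The concern.** A random effect for person alone gives every pair of visits the same correlation and every visit the same variance. Here the gaps are about 8 and 18 weeks, most participants were expected to come from the post-hospital service (Participants and setting), and the service stops between the second and third visits. Equal correlation across those gaps is possible but would be something of a coincidence. Correlation that fades with time is at least as plausible.

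If it does fade, the model averages the three correlations and applies that average to every change. The baseline-to-six-month change, whose two scores are the least correlated, then receives too small a standard error. The Background promises a comparison in both the short and the long term, and Outcome measures calls the six-month visit important. At stake is a falsely positive finding that LiFE gives a greater lasting functional gain, in a trial whose results may lead to a recommendation to change the service.

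**Working it through.** **The plan's own figure.** Sample size gives "The sample size was calculated based on 80% power, a 5% significance level and a ‘medium’ effect size of 0.5" and concludes that "a sample size of 64 in each group is indicated". Normal approximation: 2 × (1.960 + 0.842)² / 0.5² = 62.8, so 63; the t-test calculation gives 63.8, so 64. Allowing for 12% loss: 64 / 0.88 = 72.7, so 73, against about 75 stated. The figure reproduces. It does not settle the present point, because group size cancels from the ratio below.

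**Inputs.** Visits at 0, 8 and about 26 weeks come from the article. The article gives no correlations, so all of those are assumed. The SD is taken as equal at the three visits, and alpha as two-sided 5%.

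**Formula.** Let σ² be the variance at each visit and n the number per group.

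- True variance of the between-group difference in mean change: 4σ²(1 − ρ_pair)/n.
- Variance reported by a three-visit random-intercept model with arm-by-visit terms: 4σ²(1 − ρ_mean)/n, where ρ_mean averages the three pairwise correlations.
- Reported SE / true SE = √[(1 − ρ_mean)/(1 − ρ_pair)].
- Actual type I error = 2 × [1 − Φ(1.96 × ratio)].

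**Example.** With correlations 0.7 (baseline/8 weeks), 0.7 (8 weeks/6 months) and 0.5 (baseline/6 months), ρ_mean = 1.9/3 = 0.633. The ratio is √(0.367/0.5) = 0.856. Then 1.96 × 0.856 = 1.68, and the type I error is about 9.3%.

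**Baseline-to-six-month change, range of assumptions:**

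| Baseline/8 wk, 8 wk/6 mo, baseline/6 mo | SE ratio | Type I error |
|---|---|---|
| 0.70, 0.70, 0.70 (equal) | 1.000 | 5.0% |
| 0.70, 0.70, 0.60 | 0.913 | 7.4% |
| 0.80, 0.75, 0.70 | 0.913 | 7.4% |
| 0.690, 0.435, 0.300 (exponential decay) | 0.866 | 9.0% |
| 0.808, 0.619, 0.500 (exponential decay) | 0.846 | 9.7% |
| 0.934, 0.857, 0.800 (exponential decay) | 0.826 | 10.5% |

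Two other assumed patterns (0.8, 0.8, 0.6 and 0.8, 0.7, 0.5) lie just outside this range, with ratio 0.816 and 11.0%.

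**Simulation check.** 75 per group, random intercept fitted by REML, 6% missing at eight weeks and 12% at six months completely at random, 2,000 null trials per setting. The Monte Carlo standard error is about 0.5 points at 5% (√(0.05 × 0.95/2000)) and 0.7 points at 10% (√(0.10 × 0.90/2000)).

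| Correlations | Change to six months | Level at six months |
|---|---|---|
| 0.70, 0.70, 0.70 | 5.4% | 4.9% |
| 0.80, 0.70, 0.60 | 7.9% | 5.7% |
| 0.808, 0.619, 0.500 | 10.8% | 5.8% |
| 0.896, 0.781, 0.700 | 10.9% | 5.3% |

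The six-month level comparison holds up because it depends mainly on the total variance, which this model estimates well when the variances are equal. Under exponential decay the eight-week-to-six-month change is also near nominal in the closed form (5.6–5.9%).

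**The case against.** The strongest reply is that one sentence in a condensed article does not fix a three-visit model. If only the two follow-up scores are outcomes and baseline is a covariate, there is a single correlation and the unequal-correlation problem disappears. Likewise, a separate regression of change at each time point would estimate its own residual variance. This stands as a limit on the point. Still, the text lists initial data collection among the compared times, which makes baseline-as-outcome the natural reading, and nothing in it states the harmless version.

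It is also true that the size rests entirely on assumed correlations, and that it concerns one contrast among several.

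A reader might infer three stronger things, none of which the document supports.

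- **That every six-month result is too precise.** The level comparison at six months is hardly affected.
- **That the hypothesis about the longer term is tested well above 5%.** That hypothesis concerns continuing the exercise, which is recorded by calendar ticks and has no pre-programme value. What is exposed is the functional change to six months.
- **That the eight-week intention-to-treat analysis drops clients without an eight-week value.** A change score needs both values unless one is imputed, and Sample size does allow for 12% loss. But the article does not say how missing values are handled, an article commonly leaves this to the full plan, and the timing of the loss is not given. This is no finding.

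**Conclusion.** The point holds in a limited form. On the natural reading, the six-month model assumes equal variance and equal correlation across unequally spaced visits. If the baseline/six-month correlation is the lowest of the three, the standard error of the between-group difference in baseline-to-six-month change is about 9–17% too small and the type I error about 7–10.5%. If the correlations are equal, it is 5%.

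This rests on correlations that the article does not give, on equal variances, and on baseline being modelled as an outcome. The six-month level comparison stays at about 5.3–5.8% under the fading correlations simulated, and the primary eight-week test is untouched because it does not use the model. This is a weakness in a secondary analysis that is cheap to remove. It does not threaten the trial's main result.

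**What to change.** For the six-month analysis only, state that:

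- the outcomes are the eight-week and six-month scores;
- the fixed effects are arm, visit, arm-by-visit, baseline score and baseline-by-visit;
- the within-person covariance is unstructured and replaces the random intercept;
- the arm difference at six months from this model is the test of longer-term functional change.

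With two follow-up visits the unstructured covariance has three parameters (two variances and one covariance) against two for a random intercept. The baseline terms add two more fixed effects. Baseline scores are collected before randomisation, so no new data are needed. The group comparison at baseline would then be descriptive and sit outside this model. The primary eight-week analysis need not change on account of this point.

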**Discussion:**

If LiFE is more effective than the current exercise program, the evidence will be presented to the service management accompanied by the recommendation that it be adopted as the generic exercise program to be used within the restorative home care service.

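### The plan does not say that the ITT test of 8-week change in the composite decides, although the same 8-week comparison is repeated by regression and in a PP set, all at p<0.05

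*Protocol article*

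**What the plan says.** In the protocol article, the Sample size, Outcome measures and Data analysis sections agree on a single primary outcome: a composite of four physical tests. Data analysis constructs it at baseline, applies the same weights at 8 weeks, and tests its 8-week change as for every other outcome, by t-test or by Mann-Whitney when the data are not normal.

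The same section sets further analyses beside that test:

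- Two analysis sets, ITT and PP. The sentence that introduces them ends "PP) analyses will be performed" and ranks neither.
- A regression for the six-month results with person as a random effect, for an outcome that is not specified.
- Further regressions: "Multiple linear regressions will be used to identify any differences between the groups at initial data collection, eight weeks and six months". These also cover change over follow-up.

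One threshold covers them all: "A p value of <0.05 will be considered statistically significant".

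The Discussion part of the abstract states what hangs on the result: "If LiFE is more effective than the current exercise program, the evidence will be presented to the service management", together with a recommendation to adopt LiFE as the service's generic program. It does not say which result establishes this. The Background section puts both short-term and long-term effectiveness in the aim, and its first hypothesis is that LiFE will be undertaken more often than the current program.

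**The concern.** At 8 weeks the plan puts one question, whether the arms differ on the composite, through a change test and a regression on level, and does so in two populations. With no deciding result named, the 5% level used for the sample size is guaranteed for the adoption claim only if readers supply the ranking themselves. If ITT and PP disagree, or if change and level disagree, the article gives no agreed reading.

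The unranked PP set matters most. PP membership depends on what happens after randomisation. If it is defined by adherence, and adherence differs by arm as the first hypothesis expects, the PP comparison is between differently selected groups. In a superiority comparison it should not stand level with ITT.

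**Working it through.** **1. The plan's own figure.** Inputs from Sample size: "The sample size was calculated based on 80% power, a 5% significance level and a ‘medium’ effect size of 0.5".

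- Normal approximation: n = 2(1.960 + 0.842)² / 0.5² = 62.8, so 63 per group. The exact t-test gives 63.8, so 64, which matches "a sample size of 64 in each group is indicated". A one-sided test would need only 50, so the design is two-sided.
- Dropout of 12%: 64 / 0.88 = 72.7, so 73 against the stated figure of about 75. With 75 enrolled, 75 × 0.88 = 66 complete.
- Power at 64 per group is 80.1%.

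The sample size is therefore right for one two-sided test at 5%.

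**2. Assumptions not in the document.** No true effect; 66 per arm; equal variances and equal correlation r between visits, r = 0.5 to 0.85; PP a random fraction f of participants, f = 0.6 to 0.9. Random PP membership favours the plan, because it leaves out selection that differs by arm. The baseline comparison is not an efficacy test and is not counted. An unadjusted regression of 8-week change on arm repeats the t-test, so it is not counted separately.

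**3. Change test in ITT or PP.** A statistic on a random fraction f correlates √f with the full-set statistic. The bivariate normal chance of at least one p<0.05 is:

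| f | √f | at least one p<0.05 |
|---|---|---|
| 0.6 | 0.775 | 8.0% |
| 0.7 | 0.837 | 7.6% |
| 0.8 | 0.894 | 7.1% |
| 0.9 | 0.949 | 6.5% |

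Simulation (20,000 runs per setting) at f = 0.6 and 0.8 gave 6.8 to 8.2%.

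**4. Change or level at 8 weeks, ITT only.** Cov(Y8 − Y0, Y8) = 1 − r and Var(Y8 − Y0) = 2(1 − r), so the correlation between the two statistics is √((1 − r)/2): 0.50 at r = 0.5, 0.39 at r = 0.7 and 0.27 at r = 0.85. The chance of at least one p<0.05 is 9 to 10% (simulated 8.8 to 9.8%). The bound for two independent tests is 1 − 0.95² = 9.75%.

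**5. Change and level, each in ITT and PP, 8 weeks only.** Simulated chance of at least one p<0.05:

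| r | f = 0.6 | f = 0.8 | f = 0.9 |
|---|---|---|---|
| 0.5 | 13.9% | 12.6% | 11.5% |
| 0.7 | 14.5% | 13.8% | 11.7% |
| 0.85 | 15.4% | 13.4% | 12.3% |

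This is about 12 to 15%, against a bound of 1 − 0.95⁴ = 18.5% for four independent tests. Counting only results that favour LiFE, the range is 5.8 to 7.6% against a nominal 2.5%. The single ITT change test stays at about 5%.

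**6. After naming one result.** Error returns to about 5%, and 64 per group keeps 80% power. Adjusting for the baseline composite instead of testing change multiplies the variance by (1 − r²) / (2(1 − r)) = (1 + r)/2, which is 0.75, 0.85 and 0.925 at r = 0.5, 0.7 and 0.85. By contrast, making 8 weeks and six months co-primary at 2.5% each would need 78 per group, or 78 / 0.88 = 89 with dropout and 178 in total. Power at 64 per group would be 71%.

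**The case against.** The strongest reply is that the intended primary analysis can be read from the text. There is one primary outcome, its construction is described only at baseline and 8 weeks, one test of its change is given, and the sample size is for one such test, whose error is about 5%. Doing both ITT and PP is common, and an article may leave the ranking of sets to a fuller document. The random-effect regression and the multiple linear regressions may be a single follow-up model. Much of this stands, and it limits the size of the point. It does not remove it: the article itself lists overlapping 8-week analyses, gives them one threshold, and ties a practice recommendation to the outcome without saying which of them carries it.

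Three stronger readings may tempt a reader, and the document does not support them.

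- That the claim has no 5% error rate at all, with inflation of 20 to 25%. That figure counts ten tests, including six-month tests of the composite and a stand-in for the mixed model. The article describes no six-month composite, and the regressions may not be separate analyses.
- That any single positive result will be taken as success. The article states no such rule; it leaves the deciding result unnamed.
- That the plan errs because p<0.05 is reached at an observed difference of about 0.35 SD (1.979 × √(2/64)), while of 0.5 it says: "This effect size was considered sufficient to recommend a change in practice". Every design with 80% power has a critical difference of about 0.7 of its planning effect. The article does not claim that significance implies 0.5.

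**Conclusion.** The point holds in a limited form. The article identifies the primary outcome and a natural primary test, but does not say that the ITT version decides, and it repeats the 8-week comparison by regression and in a PP set at the same threshold. If any of those results could carry the recommendation, the chance of a false p<0.05 at 8 weeks is about 7 to 8% with only ITT or PP left open (6.5% if PP keeps 90% of participants), and 12 to 15% with level tests added. It is higher if six-month tests of the composite are also counted.

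These figures rest on assumed visit correlations and PP fractions, and on PP membership being unrelated to outcome. Adherence-based selection that differs by arm would add bias that they do not include. If the ITT change test is what the investigators mean to rely on, the error is about 5% and only the statement of it is lacking.

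**What to change.** Add to Data analysis:

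- The deciding result is the ITT arm difference in the composite at 8 weeks, tested two-sided at 5% and reported with its 95% CI. Adjustment for the baseline composite is preferable: the data are already collected, and it is at least as precise as the unadjusted change test. Keeping the change test would control the error equally well.
- The recommendation to adopt LiFE rests on this result.
- The six-month contrast is key secondary. PP, the other regressions and the other outcomes are supportive. The 8-week regressions need not be deleted.

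The cost is a few sentences, with no more participants and no new data. The downside is that a PP or secondary result can no longer carry the claim alone.
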